## **9.2 Randomization**

### **9.2.1 Allocation- sequence generation**

- The allocation sequence is based on computer-generated random numbers, and will be generated by an independent statistician
- the allocation ratio is 1 (equal probabilities to placebo and treatment)
- No stratification.

### **9.2.2 Allocation- procedure to randomize a patient**

The midwife in charge of the patients in labor will enroll eligible participants. The participants will be assigned to treatment based on prespecified allocation envelopes with consecutive numbers that are kept in a locked room in the maternity ward, which is a separate ward on a different floor than the delivery ward. The numbered envelopes contain information about what IMP to prepare. When the midwife in charge on the maternity ward opens the envelope, the allocated treatment is revealed. The midwife in charge on the maternity ward is the only person who will know which treatment is given. After the allocated treatment is revealed, the midwife seals the envelope, and labels the envelope with the participant's name and date of birth.

Only personnel authorized by the principal investigator for preparing treatment will have access to treatment allocation, and the allocation will not be available until the patient has signed the informed consent form and deemed eligible to participate in the study. That is, authorized personnel will only know the allocation of included patients, but not for future patients. Once the patient has been included, the midwife in charge authorized for treatment preparation will reveal the allocation. Further procedure will be as follows:

1. Prepare the allocated treatment for administration
2. Stick the participant's name tag next to the unique allocation number on the prespecified allocation list
3. Sign the allocation list
4. Prepare and append label to the IMP in the same way that we do in clinical practice, with patient name, data of birth and allocated trial number
5. Dispatch all packaging identifying the allocated treatment
6. Lock the room with the envelopes to prevent blinded site staff knowledge of allocation
7. A third person, blinded to the content of the IMP, will bring the IMP from the maternity ward to the delivery ward

Site staff should take measures to maintain the blinding, e.g. not storing medication such that it is evident which treatment has been given by identifying missing medication.

All patients and all labor ward personnel taking care of the patients during labor and birth, the investigators, the data analyst and the statistician will be blinded. The treatment drug or placebo will be prepared by the midwife in charge at the maternity ward, once a patient is included in the study. The midwife in charge on the maternity ward will not be involved in the delivery at any time. The midwife in charge on the maternity ward will be the only person not blinded.

The midwife in charge on the maternity ward will give the prepared IMP to a third person, who is blinded, and will give the IMP to the midwife on duty who takes care of the participant.

In the event of an SAE, the Investigator may only break the treatment code if the appropriate management of the patient necessitates immediate knowledge of the current treatment (in case of severe anaphylactic reactions). Although it is advantageous to retain the blind for all patients prior to final trial analysis, when an SAE may be a serious adverse reaction unexpected or otherwise judged reportable on an expedited basis, it is recommended that the blind should be broken only for that specific patient, by the CTU, even if the Investigator has not broken the blinding.

Unblinding of the treatment allocation is permissible only if the safety and well-being of the patient is being compromised. The decision to reveal the treatment allocation during the study may only be done by the principal investigator or the attending physician on duty. If the doctors are delayed, and the SAE is considered to be life-threatening, the midwife in charge can decide to reveal the treatment allocation. If neither the doctor nor the midwife in charge is available, the midwife on duty who takes care of the participant may open the envelope to reveal the allocation. In this way, only the allocation for the involved participant will be revealed. The date and time of un-blinding must be documented in the eCRF and in the patient's hospital records.

### 9.3 Population for Analysis

The following populations will be considered for the analyses:

- Intention to treat (ITT) population: All randomized participants, regardless of protocol adherence.
- Per-protocol population (PP): Includes all participants who have followed the protocol, i.e. one dose of the study medication (IMP). Randomized patients who were not eligible are excluded.
- Safety population: Includes all participants who have received one dose of study medication IMP. Participants who withdraw from the study will be included in the safety analysis. A list of withdrawn participants, preferably with the reasons for withdrawal, will be made.

The primary population is the ITT population.

### 9.4 Planned analyses

The main statistical analysis is planned when

- The planned number of patients has been included

- All included patients have either finalized their last assessment or have/are withdrawn according to protocol procedures
- All data have been entered, verified and validated according to the data management plan

Prior to the main statistical analysis, the data base will be locked for further entering or altering of data. A separate statistical analysis plan (SAP) will provide further details on the planned statistical analyses. The SAP will be finalized, signed and dated prior to database lock. The treatment allocation will be revealed after the database lock and used in the statistical analysis.

No interim analysis is planned.

Deviation from the original statistical plan will be described and justified in the Clinical Study Report. Amendments to plan can be done until day of DB lock.

## 9.5 Statistical Analysis

We will make a SAP as a separate document that fully details the planned analyses. The statistical analyses will be pre-specified in full detail in the SAP.

### 9.5.1 Primary analysis

This protocol is designed to address a single primary endpoint, which is the duration of labor from when the participant was given IMP, to delivery

This is a time-to-event outcome, where vaginal delivery is the event of interest and emergency cesarean delivery is the censoring event.

The study is designed to establish the superiority of intravenously administered Butylscopolamine bromide compared to placebo on a single primary endpoint; the duration of labor from when the participant was given IMP, to delivery. The null hypothesis is that there is no difference in the duration of labor from when the participant was given IMP, to delivery, between the two treatment groups.

The alternative hypothesis is that there is a difference in the duration of labor from when the participant was given IMP, to delivery, between the two treatment groups.

Superiority of Butylscopolamine bromide on the duration of labor from when the participant was given IMP, to delivery, is claimed if the primary null hypothesis is rejected, and the group difference is in favor of Butylscopolamine bromide.

Statistical significance is claimed if the null hypothesis is rejected on the significance level (alpha) of 0.05 (two-sided). That is, if the p-value of the null hypothesis test is less than or equal to 0.05.

As there is only one identified primary analysis, there will be no adjustments for multiple testing in the secondary analyses. Secondary analyses on secondary endpoints will be regarded as supportive.

The primary endpoint will be analyzed using Weibull regression, and the p-value for the statistical hypothesis test for the primary endpoint will be the p-value from this analysis. Unadjusted Kaplan-Meier plots will be presented. The effect measures will include median (and quartiles) duration in the two treatment groups, and the proportion of women who give birth within 2, 4, 6, 8, 10 and 12

hours after randomization. All efficacy analyses will be presented by the size (point estimate) of the difference between the treatments and the associated 95% confidence interval.

The statistical analyses will be done in SPSS v23, or R version 3.5.0 (<https://www.r-project.org/>).

Robustness of the results will be checked using Cox regression, by including baseline characteristics known to be associated with labor duration as covariates, and performing the analyses with different options for data imputation.

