| Kirim (26)   | 20 iv    | Published after Cochrane review | Turkey  | Journal of Maternal, Fetal and Neon. Med. | 387/mix       | 57 minutes |

The study treatment will be administered to the woman by authorized site personnel only.

IMP must be given as soon as possible after randomization. If IMP is given more than 45 minutes after randomization, the midwife must check the cervical dilatation again before IMP is given.

The intravenous injection should be performed 'slowly' (in rare cases a marked drop in blood pressure and even shock may be produced by Buscopan).

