### **5.4 Procedures for Discontinuation**

#### **5.4.1 Patient Discontinuation**

All patients randomized will be included in the study population.

Patients who are randomized in spite of not fulfilling all of the inclusion criteria or fulfilling one or several exclusion criteria can be replaced. Patients who withdraw from the study after randomization cannot be replaced.

If the patient consents, end of study information will be obtained and recorded.

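### The primary endpoint is timed from IMP, but its 2-12 hour proportions are timed from randomization, and the all-randomized primary population has no start time for a woman who is not dosed

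*Protocol*

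**What the plan says.** **Endpoint.** Protocol section 9.5.1 reads: "This protocol is designed to address a single primary endpoint, which is the duration of labor from when the participant was given IMP, to delivery". Both hypotheses and the superiority claim in that section repeat this origin. The synopsis and sections 1.7 and 6.1 agree with it.

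**Effect measures.** The same section lists, after the median and quartiles, "the proportion of women who give birth within 2, 4, 6, 8, 10 and 12"; the sentence goes on to count these in "hours after randomization".

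**Population.** Section 9.3 defines "Intention to treat (ITT) population: All randomized participants, regardless of protocol adherence" and adds: "The primary population is the ITT population". Section 5.4.1 agrees: "All patients randomized will be included in the study population". Section 9.3 also defines a set by receipt of drug: "Safety population: Includes all participants who have received one dose of study medication IMP".

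**Gap between the two origins.** Section 4.2 asks for IMP as soon as possible after randomization but sets no upper limit: "If IMP is given more than 45 minutes after randomization, the midwife must check the cervical dilatation again before IMP is given". Section 9.1 treats the origins as different. It notes that the source trial for the sample size timed labor from randomization, whereas this trial times it from IMP.

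**The concern.** Two parts of the plan do not fit together.

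First, section 9.5.1 reports one endpoint on two clocks. The model, the curves and the medians start at IMP, while the 2-12 hour proportions start at randomization. A reader would expect the proportion delivered by 4 hours to be readable from the Kaplan-Meier curve at 4 hours. As written, it is not.

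Second, the endpoint exists only for dosed women, but the primary population includes every randomized woman. The protocol allows for randomized women who are not dosed: the safety set is defined separately by receipt of a dose, section 5.3 lists incorrect enrolment and voluntary discontinuation as reasons to stop a treatment that consists of one injection, and section 5.4.1 covers withdrawal after randomization. No section gives such a woman a start time. Followed literally, she drops out, and the analysis called ITT is done on dosed women only.

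At stake are the consistency of the reported results and a correct description of who is in the primary analysis.

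**Working it through.** **1. The protocol's own figure.** Inputs from sections 9.1 and 9.5.1: difference 1 h, SD 2.8 h, two-sided alpha 0.05, power 80%. Allocation is 1:1 (section 9.2.1).

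n per arm = 2(z₀.₉₇₅ + z₀.₈₀)²σ²/δ² = 2 × (1.960 + 0.842)² × 2.8² / 1² = 123.1, rounded up to 124 (248 in total).

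The protocol gives 123 per group (246), which has power 79.98%. The figure reproduces to within rounding. With the planned 250 (125 per arm), power is Φ(1/(2.8 × √(2/125)) − 1.960) = 80.6%.

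The SD of 2.8 h was itself measured from randomization (section 9.1). Moving the origin to randomization therefore leaves the required number at 248.

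**2. Size of the mismatch in the proportions.** The protocol gives no distribution for the delay from randomization to IMP, so the delay d is assumed, and taken as the same for every woman. A Weibull is matched to mean 5.2 h and SD 2.8 h, with that duration taken to run from IMP and cesarean censoring ignored:

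- Solve √(Γ(1+2/k)/Γ(1+1/k)² − 1) = 2.8/5.2, which gives shape k = 1.935.
- Scale λ = 5.2/Γ(1+1/k) = 5.863 h.
- Delivered within t hours of IMP: F(t) = 1 − exp(−(t/λ)^k). Delivered within t hours of randomization: F(t − d).

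For example, F(4) = 37.9% and F(3.5) = 30.8%, a gap of 7.1 points.

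| Hours | From IMP | From randomization, d = 15 min | d = 30 min | d = 45 min | d = 60 min |
|---|---|---|---|---|---|
| 2 | 11.7% | 9.2% | 6.9% | 4.9% | 3.2% |
| 4 | 37.9% | 34.4% | 30.8% | 27.3% | 23.9% |
| 6 | 64.9% | 61.8% | 58.7% | 55.4% | 52.0% |
| 8 | 83.9% | 82.0% | 80.0% | 77.9% | 75.6% |
| 10 | 94.0% | 93.1% | 92.1% | 91.1% | 89.9% |
| 12 | 98.2% | 97.8% | 97.5% | 97.1% | 96.6% |

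Of the listed time points, 4 hours shows the largest gap: about 3.5, 7, 11 and 14 points for the four delays. At 8 hours a 30-minute delay gives 3.9 points, and at 12 hours less than 1.

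**3. Size of the undosed problem.** The share never dosed is not stated, so 2%, 5% and 10% of 250 (about 5, 12 and 25 women) are assumed. Power uses the formula in step 1. If these women drop out, n falls. If they are kept from randomization with no drug effect, n stays at 125 per arm and δ becomes 1 × (1 − share).

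| Assumed undosed share | Women | Power if dropped | Power if kept, no effect in them |
|---|---|---|---|
| 0% | 0 | 80.6% | 80.6% |
| 2% | 5 | 79.8% | 79.0% |
| 5% | 12 | 78.7% | 76.5% |
| 10% | 25 | 76.4% | 71.9% |

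**The case against.** The strongest defence is that the decisive result is hardly touched. The p-value comes only from the Weibull regression, whose origin is stated consistently as IMP; the wording about randomization affects only the proportions. The IMP origin is a deliberate choice. One intravenous dose is given promptly, and section 4.6 expects no compliance problem. The re-examination rule in section 4.2 concerns women dosed late, not women left undosed. A separate SAP, not shown here, is meant to carry the detail. Much of this stands, and it limits the point.

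A reader might infer more than the documents support:

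- **That the ITT analysis cannot be run.** It fails only for women randomized but never dosed. If every woman is dosed, it runs.
- **That undosed women are mostly the fastest labors.** The protocol does not say so. Women enter because labor is slow, and undosed women could equally be withdrawals or found ineligible.
- **That this is a biased as-dosed analysis.** Women would still be compared by allocated arm, so the set is a modified ITT. Patients, labor ward staff and investigators are blinded, and the one unblinded midwife takes no part in the delivery (section 9.2), so delay and non-dosing should be similar in both arms.
- **That results are off by 7 to 11 points.** Those figures delay every woman by 30 or 45 minutes and use the worst time point. They are shifts in level, expected to be similar in both arms, not shifts in the treatment difference.

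The appeal to the SAP does not dispose of the point. The protocol itself fixes the endpoint, the population and the origin of the proportions, so a SAP has to depart from one of them. The data imputation mentioned in section 9.5.1 is only a robustness check and does not give a start time to a dose that was never given.

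**Conclusion.** The inconsistency is real and lies in text that the protocol fixes. The mismatch of origins stands even if every woman is dosed, as long as there is some delay between randomization and IMP. The population problem arises only if at least one randomized woman is not dosed, which the protocol allows for without giving a frequency.

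The expected harm is threefold: proportions that disagree with the curves beside them, by roughly 3.5 to 11 points at 4 hours under assumed uniform delays of 15 to 45 minutes; a primary set labelled ITT that may hold dosed women only; and a small loss of precision, with power falling from 80.6% to 79.8-78.7% if an assumed 2-5% drop out. Clear bias between arms is not shown, and the sample size is unaffected. This should be fixed, and settled before unblinding because it decides who is in the primary analysis.

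**What to change.** Use one origin throughout, by one of two routes.

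(a) **Randomization.** Start the clock at randomization for all randomized women in the Weibull model, the Kaplan-Meier curves, the medians and the 2-12 hour proportions. Report IMP-to-delivery as a supportive analysis in dosed women. This keeps a true ITT set and matches the origin of the SD used for the sample size. Costs: the short, blinded delay is added to both arms; undosed women dilute the effect (last column of the second table); and the endpoint wording has to change wherever it appears (synopsis, 1.7, 6.1, 9.1, 9.5.1), which needs a protocol amendment under section 10.3.

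(b) **IMP.** Keep the endpoint as worded. In section 9.3, name the primary set as a modified ITT of randomized and dosed women, analysed by allocated arm. Report the number undosed by arm, and add a from-randomization sensitivity analysis in all randomized women. In section 9.5.1, count the proportions from IMP. Costs: fewer edits, but the primary analysis no longer covers all randomized women and must say so.

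Do not give undosed women a randomization origin while dosed women keep the IMP origin: that would put two clocks inside the one endpoint.

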Maternal: Common ( $\geq 1/100$  to  $< 1/10$ ): Gastrointestinal: Dryness in the mouth. Cardiology: Tachycardia, dizziness. Ophtalmology: Accomodation disturbance. Unknown frequency: Cardiology: Hypotension, flushing. Skin: Dyshidrosis. Immune system: Anaphylactic shock, anaphylactic reactions, dyspnea, skin reactions including urticarial, rash, erythema and itching. Other forms of hypersensitivity. Kidney: Urinary retention. Ophtalmology: Mydriasis, increased intraocular pressure. Rare cases with serious skin reactions like Steven-Johnsons syndrome have been reported.

According to WHO recommendations for augmentation of labor based on the Cochrane review from 2013 (22),(31), there are 5 RCTs comparing Buscopan with placebo including altogether 845 newborns with no differences in transfer to the Neonatal Intensive Care Unit. One RCT with 100 fetuses did not show any differences in prevalence of fetal distress. One RCT with 130 fetuses did not show any difference in fetal bradycardia, and two RCTs with 230 fetuses did not show any difference in fetal tachycardia. None of the 17 RCTs in the Cochrane review reported any side effects related to Buscopan (22).

Women who are allocated to the control group will contribute to answer an important medical question for future laboring women and their children. They will need an IV access, which could be considered a down side. However, it is routine procedure in the hospital to establish an IV line

when there is labor dystocia. The IV access may be an advantage if they women augmentation with oxytocin or if something unexpected happens.

Women who are allocated to the intervention group may experience a shorter labor if the IMP has the presumed effect. In that case, they will receive less oxytocin, and experience fewer oxytocin side effects. Based on previous studies, the reduction in the active phase of labor will be approximately one hour. This reduction will take place in the first stage (opening phase), and not the second stage of labor (expulsion phase).

Based on data from our department, 72% of primiparous women who crossed the alert line (the inclusion criterion of this study) of the partogram received augmentation with oxytocin with an average duration of 214 minutes. Of the women who crossed the alert line, 15% delivered by cesarean section and 25% had an operative vaginal delivery, compared to 2% and 16% among women with normal progress in labor, respectively.

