### **1.7 Primary Endpoint**

#### **Primary endpoint:**

Duration of labor from the time when the participant was given IMP to delivery

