A methodological issue is that while both the articles we use as a basis for the sample calculations report means and SDs for the duration of labor, this outcome is a time-to-event outcome, with emergency cesarean delivery as a censoring event. The primary outcome will be treated as such in the analyses, and this should also be reflected in the power calculation. However, background data on our primary endpoint are hard to find, and we have therefore based our sample size calculation on the results from Dencker et al.

In the study population, the expected proportion of emergency cesarean delivery will be approximately 7%. Hence, most (approximately 93%) duration times will be observed, and a sample size based on a traditional continuous outcome e.g. a two-sample t-test will give a good indication for the sample size. Due to the inherent skewness of labor duration data, one can expect published values of SD to be slightly overestimated.

With the SD of 2.8 given in Dencker et al., and a power of 80 % we would need in total 246 women (123 women in each group) to discover a difference of 60 minutes. Furthermore, we calculate that

we will need written informed consent from at least 600 women to be able to randomize approximately 250 participants (8% [50 women] will be lost because of elective cesarean section, 25% [140 women] will be induced or receive oxytocin before 3 cm, and 40% [165 women] will not cross the alert line). In addition some of the eligible women will not be randomized because the midwife on duty forget to take the necessary steps and some participants will withdraw from the study.

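### The primary endpoint is worded as time to delivery but censors emergency cesarean, so absolute results from the planned models would match neither vaginal delivery nor birth by any mode

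*Protocol*

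**What the plan says.** Section 1.7 of the protocol gives the primary endpoint as "Duration of labor from the time when the participant was given IMP to delivery". No mode of delivery is excluded.

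Section 9.5.1 then narrows the event: "This is a time-to-event outcome, where vaginal delivery is the event of interest and emergency cesarean delivery is the censoring event". Section 9.1 repeats the rule: "this outcome is a time-to-event outcome, with emergency cesarean delivery as a censoring event". It is therefore a stated choice and not a detail left to the SAP.

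On analysis and reporting, section 9.5.1 says "The primary endpoint will be analyzed using Weibull regression" and "Unadjusted Kaplan-Meier plots will be presented". The effect measures are medians, quartiles and "the proportion of women who give birth within 2, 4, 6, 8, 10 and 12" hours. The robustness checks named are Cox regression, covariate adjustment and different imputation options; none changes the censoring rule. Section 9.5.2 carries the approach over to the secondary time-to-event endpoints.

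Two cesarean rates appear. Section 9.1 expects about 7% in the study population. Section 1.5 reports from the department's own data: "Of the women who crossed the alert line, 15% delivered by cesarean section and 25% had an operative vaginal delivery". The corresponding cesarean figure for women with normal progress is 2%.

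**The concern.** Censoring suits a woman whose event has not yet been seen but could still occur. After a cesarean, vaginal delivery cannot occur. One minus Kaplan-Meier with cesareans censored estimates the proportion delivered vaginally in a setting where cesareans do not happen, and even that needs women who have a cesarean to resemble those still in labor. The 15% against 2% contrast in section 1.5, and the listing of labor dystocia as an indication for operative delivery in section 1.8, make that doubtful.

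The stake is the absolute results for the only primary endpoint. A reader of the report will take the proportion who give birth within 12 hours as a count of births, or perhaps of vaginal births. An estimate with cesareans censored is neither. If the choice between the two readings is left until allocation is known, it becomes post hoc.

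**Working it through.** **The plan's own figure.** Section 9.1 gives 246 women for a 60-minute difference, SD 2.8 h and 80% power. With two-sided alpha 0.05, n per group = 2 × (1.960 + 0.842)² × 2.8² / 1.0² = 123.07, so 246 is reproduced to rounding. Cesarean handling does not alter this figure. With 250 enrolled, the expected vaginal deliveries are 250 × 0.93 = 232.5 or 250 × 0.85 = 212.5.

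**Inputs.** From section 9.1: mean 5.2 h, SD 2.8 h, cesarean 7%. From section 1.5: cesarean 15%. Assumed, because the protocol does not give them: a Weibull form with that mean and SD for the cause-specific time to vaginal delivery (shape 1.935, scale 5.863 h), and the timing of cesareans. Three timings were tried, each calibrated to 7% or 15% overall: cesarean hazard proportional to the vaginal-delivery hazard, constant, and late (rising with the cube of time).

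**Formulas.** Let H(t) = (t/5.863)^1.935 be the vaginal cumulative hazard, h(t) its derivative, and G(t) the cesarean cumulative hazard.
- One minus Kaplan-Meier: 1 − exp(−H(t)).
- Vaginal cumulative incidence: the integral from 0 to t of h(u) exp(−H(u) − G(u)) du.
- Any-mode delivery: 1 − exp(−H(t) − G(t)).

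**Check by hand (proportional timing, 12 h).** H(12) = 4.00, so 1−KM = 98.2%. With proportion p having a cesarean, the vaginal cumulative incidence is (1 − p)[1 − exp(−H/(1 − p))]. For p = 0.07 this is 0.93 × (1 − exp(−4.30)) = 91.7%. For p = 0.15 it is 0.85 × (1 − exp(−4.71)) = 84.2%.

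**Results over the three timings** (percentage points; differences taken before rounding).

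| Hours | 1−KM, % | Excess over vaginal, 7% | Excess over vaginal, 15% | Shortfall vs any mode, 7% | Shortfall vs any mode, 15% |
|---|---|---|---|---|---|
| 2 | 11.7 | 0.0-0.2 | 0.0-0.5 | 0.0-2.5 | 0.1-5.5 |
| 4 | 37.9 | 0.1-1.3 | 0.3-2.9 | 0.5-3.4 | 1.5-7.5 |
| 6 | 64.9 | 0.7-3.1 | 1.9-6.9 | 1.5-2.9 | 4.1-6.1 |
| 8 | 83.9 | 2.2-4.9 | 5.7-10.6 | 1.7-2.1 | 3.6-5.2 |
| 10 | 94.0 | 4.2-6.1 | 10.2-13.1 | 0.8-1.8 | 1.6-3.7 |
| 12 | 98.2 | 5.8-6.7 | 13.3-14.4 | 0.3-0.9 | 0.6-1.6 |

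Median: 4.85 h by Kaplan-Meier. For vaginal delivery it is 4.87-5.01 h (7%) or 4.91-5.24 h (15%), so Kaplan-Meier is 0.02-0.16 h or 0.05-0.39 h too short. For any-mode delivery it is 4.61-4.79 h or 4.32-4.68 h, so Kaplan-Meier is 0.07-0.24 h or 0.17-0.53 h too long. Upper quartile: 6.94 h by Kaplan-Meier against 7.09-7.43 h (7%) or 7.43-8.34 h (15%) for vaginal delivery.

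**Dependence on latent duration.** When cesareans were drawn only from the longest 30% of latent durations, 1−KM at 12 h was 97.7% against 91.6% delivered vaginally (7%), and 96.5% against 84.1% (15%). The gaps, 6.1 and 12.4 points, are similar.

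**Between arms.** Assume means of 5.2 and 4.2 h, a common shape and equal cesarean rates. The difference in medians is 0.93 h by Kaplan-Meier against 0.94-0.96 h (7%) or 0.94-1.01 h (15%) by vaginal cumulative incidence. At 12 h the difference in proportions is 1.6 points against 0.6-1.3 or 0.1-1.1. The largest discrepancy is at 8 h: about 2 points at 7% and about 4 at 15%.

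**The case against.** The strongest reply has four parts.

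- **Source of the figures.** Section 9.5.1 mentions the Kaplan-Meier plots in one sentence and the medians and proportions in the next, without saying that the latter come from the former. With nearly every woman delivered within hours, the proportions could be simple counts, and the SAP may say so. This stands as a limit on certainty. It does not settle which births would be counted, because the endpoint and event definitions disagree.
- **Size.** Large single-arm gaps shrink in the between-arm difference, which section 9.5.1 says will be reported. This stands while cesarean rates are equal by arm. The discrepancy would be larger if the rates differed.
- **Cesareans are examined elsewhere.** A reader might infer that a drug effect on cesareans would go unseen. It would not show in the primary result, but vaginal versus cesarean delivery is a secondary endpoint (section 1.7) compared by arm (section 9.5.2), so the trial as a whole would not miss it.
- **Validity of the test.** A reader might also infer that the primary p-value is invalid. Weibull regression with cesareans censored still compares the cause-specific rate of vaginal delivery between arms, so the documents do not support that inference.

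**Conclusion.** The endpoint wording and the event definition conflict, and the censoring rule gives absolute estimates that fit neither meaning of birth. It is tempting to say simply that the plan overstates delivery. That holds only for vaginal delivery; for women who give birth by any mode, the same estimate is too low.

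Against vaginal delivery the error sits mainly in the upper quartile and the 8-12 h proportions, and is small at 2-4 h and for the median. Against any-mode birth the error can peak earlier, at 4 h if the cesarean hazard is constant. These sizes rest on the assumed Weibull form and cesarean timings, and on which of the protocol's two cesarean rates applies. The late gap depends little on timing: as the Kaplan-Meier estimate nears 100%, the vaginal cumulative incidence levels off at 93% or 85%, so the gap approaches the cesarean proportion itself.

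The sample size and the primary test are not put in doubt by this point. What needs correcting is the definition of the event and the estimator for the absolute effect measures.

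**What to change.** Before database lock, state in section 9.5.1 and the SAP whether the event is vaginal delivery or delivery by any mode.

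- **If vaginal delivery:** name the endpoint time to vaginal delivery throughout. Label the Weibull model cause-specific and keep it for the primary p-value. Report curves, medians, quartiles and 2-12 h proportions as Aalen-Johansen cumulative incidence with cesarean as a competing event, and show cesarean incidence by arm alongside.
- **If any mode:** count cesarean as an event; Kaplan-Meier then matches the wording about giving birth.

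Apply the same decision to the secondary endpoint that runs from onset of active labor to delivery, and reconcile the 7% and 15% cesarean rates, since the gap scales with them. A Fine-Gray sensitivity analysis is optional.

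The cost is a change of wording and a little more analysis, with no extra participants or data. The downside under the vaginal-delivery option is that the reported proportions will look less favourable than Kaplan-Meier figures.
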